### Study Timeline

This study will have a screening/baseline assessment period of 21 days (maximum) with three sessions spaced at least 48 h apart, a 12-week exercise training period, and a post-intervention assessment period of 10 days (maximum) with two sessions spaced at least 48 h apart. Subjects will visit Ohio University's Clinical and Translational Research Unit facilities prior to the intervention for baseline assessments. During Visit 1 we will obtain informed consent and conduct a full medical history screening and a short physical performance battery (SPPB) (53) to determine if candidates meet the inclusion/exclusion criteria. Subjects who meet the criteria will be enrolled in the study and complete a series of clinical and physiological outcome measures over the three baseline visits. Upon completion of baseline assessments, subjects will be randomized into one of the three exercise groups for the 12-week exercise intervention. All exercises will be performed on site and supervised by an exercise professional 3 days per week. All baseline assessments will be repeated upon completion of the exercise intervention. A table of events for the study is illustrated in Table 2.

**Table 2 T2:** Schedule of events for all groups.

	**Baseline period**			**Exercise intervention**		**Follow-up**	
	**Visit 1^**c**^**	**Visit 2^**c**^**	**Visit 3^**c**^**	**Sessions 1–35^**a**^**	**Session 36 (visit 4)^**b**^**	**Visit 5^**d**^**	**Visit 6^**d**^**
Day (window)	−21 to −5	−19 to −3	−17 to −1	1 to 84	80 to 83	84 to 92	86 to 94
**SCREENING/BASELINE:**							
Informed consent	X						
Medical history	X						
Inclusion/exclusion	X						
Demographics	X						
Vitals	X						
Height and weight	X						
**SURVEYS:**							
PASE	X						
MMSE	X						
SEE	X						
**EXERCISE SESSIONS:**							
Exercise				X	X		
**FUNCTIONAL TASKS:**							
4SST	X				X		
Six-min walk	X				X		
SPPB	X				X		
Stair climb	X				X		
Grip strength	X				X		
**MEDICAL IMAGING:**							
MRI		X				X	
DXA		X				X	
**CARDIORESPIRATORY:**							
GXT		X				X	
**MUSCULAR TESTING:**							
MVC			X				X
Ballistic			X				X
Twitch force			X				X
VA			X				X
Isokinetic power			X				X
Isokinetic fatigue			X				X
**RANDOMIZATION**			X				

a *Exercise training sessions will be performed three times per week with at least 1 day between sessions, and no more than two exercise sessions on consecutive days in the same week*.

b *Post-intervention functional task testing will be performed immediately prior to the final exercise training session (session 36)*.

c *Baseline testing will be completed within 21 days of Visit 1, with at least 2 days between testing sessions*.

d *Post-intervention testing will be completed within 10 days of the final exercise session, with at least 2 days between testing sessions. 4SST, 4-square step test; DXA, dual-energy X-ray Absorptiometry; GXT, graded exercise test; MMSE, mini-mental state examination; MRI, magnetic resonance imaging; MVC, maximal voluntary contraction; PASE, physical activity scale for the elderly; SEE, self-efficacy for exercise scale; SPPB, short physical performance battery; VA, voluntary activation*.

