### Study Subjects

A minimum of 24 (and up to 30) subjects aged 60–75 years of age that are generally healthy but sedentary will be recruited, enrolled, and randomized in this study (*n* = 8–10 per group). Potential subjects will be recruited from the local community by way of flyers, community events, or emails to individuals who have previously participated in studies with the Ohio Musculoskeletal and Neurological Institute at Ohio University in Athens, Ohio, USA. All interested individuals will complete a pre-screening phone interview, and all that are not ruled ineligible will be invited for in-person screening. Written informed consent will be obtained from each subject in accordance with the Declaration of Helsinki. Ethical Approval for this study has been obtained from the Ohio University Institutional Review Board (protocol number 18-F-55).

Eligible subjects will be insufficiently active. We define “insufficiently active” as not meeting either the endurance or resistance exercise recommendations for older adults, as set forth by the American College of Sports Medicine (ACSM), for three consecutive months. The current ACSM recommendations for endurance training are 150–300 min per week of moderate-intensity activity (perceived exertion of 5–6 on 0–10 scale), or 75–150 min per week of vigorous-intensity activities (perceived exertion of 7–8 on 0–10 scale) (15). The recommendations for resistance training are at least 2 days per week of progressive weight training activities that use the major muscle groups (perceived exertion of 5–8 on 0–10 scale) (15). Additionally, the subjects must not be highly active outside of a structured exercise program (i.e., consistent hard physical labor). They must also have a 6-min walk distance within a normal range for adults aged 60–75. We calculated a normal 6-min walk range by averaging 6-min walk values from multiple studies, plus or minus one standard deviation (45–48). The calculated 6-min walk range for females was 400–675 meters, and for males was 450–725 meters. Table 1 describes inclusion and exclusion criteria in detail. These criteria are designed to recruit a generally healthy, but insufficiently active population, and exclude individuals with poor health and physical function where there could be concerns about a subject's ability to appropriately perform the testing and exercise prescription.

**Table 1 T1:** Inclusion and exclusion criteria.

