### Exercise Intervention

Each subject will perform their prescribed exercise three times per week for 12 weeks. Time between visits will generally be 48–72 h, but may range from 24 to 96 h to meet the demands of the subject's schedule. Subjects may be allowed to exercise on consecutive days one time per week, but must have at least 48 h before a third exercise session is completed (for example, Monday, Tuesday, Thursday is acceptable, but Monday, Tuesday, Wednesday is not). Prior to each exercise session an exercise supervisor will perform a brief medical safety check. If the subject reports changes in health status that are concerning, has abnormal vital signs (blood pressure readings that exceed 170 mmHg for systolic blood pressure or 100 mmHg for diastolic blood pressure), or has changed medications/dosage, they will not be allowed to continue exercising until the study physician has reviewed the changes and clears the subject. After the medical safety check, the subject will perform a 5-min warm-up on the stationary bike at a low intensity (i.e., output 50% or less of their maximal output during the GXT). After the subject has completed the prescribed exercise for the day they will perform a 5-min cooldown at a low intensity on the stationary bicycle. For the RT and MICT exercise protocols we will employ a pragmatic trial design that follow the recommendations set forth by the ACSM, but that are not necessarily matched by time. There are currently no recommendations for HIIT in older adults, and the exercise sessions are shorter in duration due to the high-intensity nature.

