#### Adherence

Successful adherence will be defined as a study subject who achieves at least an 80% adherence rate (i.e., attends 29 of 36 exercise sessions).

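### Post-intervention functional tests are placed before the last training session with no minimum rest set, so arm-dependent residual fatigue in those change scores cannot be excluded, and the text and Table 2 disagree on the timing

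*Protocol article*

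**What the plan says.** **When the functional tests are repeated.** Study Timeline: "All baseline assessments will be repeated upon completion of the exercise intervention". The same section describes a post-intervention period with two sessions, and the Abstract also places the repeat assessments after the intervention. Table 2 puts the repeat 6-min walk, SPPB, 4SST, stair climb and grip tests at Visit 4, which is session 36. Footnote b says: "Post-intervention functional task testing will be performed immediately prior to the final exercise training session (session 36".

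**Spacing of training sessions.** Exercise Intervention: "Time between visits will generally be 48–72 h, but may range from 24 to 96 h". It adds: "Subjects may be allowed to exercise on consecutive days one time per week", with the condition that subjects "must have at least 48 h before a third exercise session is completed". Table 2, footnote a, reads: "Exercise training sessions will be performed three times per week with at least 1 day between sessions". The same footnote then allows up to two sessions on consecutive days in a week.

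**Spacing of test visits.** Baseline visits are at least 48 h apart, and so are the two follow-up visits (Study Timeline; Table 2, footnotes c and d).

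**State at baseline.** Functional tests are done at Visit 1, before randomization. Study Subjects: "Eligible subjects will be insufficiently active".

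**Use in the analysis.** Six-min walk is analysed as absolute change from baseline, compared between the three arms by one-way ANOVA (Statistical Methods). Stair climb, 4SST and grip are listed under Other Outcomes and also use change from baseline. SPPB is retested but is not listed as an outcome.

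**The concern.** A change score is meant to capture the adaptation to 12 weeks of training. If the second test follows closely on a training bout, the score also contains whatever fatigue or soreness that bout left behind. The baseline test has no counterpart, because nobody has trained in the study by then.

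The timing rule is the same for all arms, but the bout that precedes the test is not. One arm comes from resistance exercise, one from steady cycling and one from cycling intervals. If recovery from these differs, the difference enters the between-arm comparison of walk distance and the other functional outcomes. The rule also lets participants within an arm be tested anywhere from about one to four days after training, which can add variation.

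Separately, a reader of the Abstract and the Study Timeline would believe that these tests were done after training had ended. Table 2 says otherwise.

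**Working it through.** The plan states no figure on this point, so there is nothing to reproduce. The check sets the provisions side by side.

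1. **Order of events.** The Study Timeline places the repeat of all baseline assessments after the intervention, in two sessions. Table 2 has those two sessions as Visits 5 (days 84 to 92) and 6 (days 86 to 94). The functional tests are in neither. They are at Visit 4 (days 80 to 83), before session 36. For these tests the statements conflict.

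2. **Shortest gap before the test.** A week of Monday, Thursday, Friday has gaps of 72 h and 24 h. It contains one consecutive-day pair and stays within the 24 to 96 h range. The 48 h condition is written as a limit on what follows a consecutive pair, and the protocol's own example places the pair first. Here the pair is sessions 35 and 36, so the test falls about 24 h after session 35. The day windows do not prevent this: the window for sessions 1–35 runs to day 84 and overlaps the Visit 4 window.

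3. **Footnote a.** If one day between sessions means a rest day, the footnote contradicts its own allowance of consecutive days and the 24 h minimum in Exercise Intervention. If it means 24 h, the three agree. The wording does not settle which.

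4. **The preceding bout, by arm** (weeks 9–12; session 35 durations from Table 5):
   - RT: ten exercises, 70% of them for the legs, 3–5 sets at RPE 7–8.
   - MICT: 45 min at 70–75% of heart rate reserve.
   - HIIT: 30 min, with about 10 min at high intensity, at 85–100% of heart rate reserve.

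   All three load the legs. They differ in type, length and intensity, and nothing in the protocol ranks them by recovery time.

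5. **Sensitivity, by assumption only.** The document gives no SD for the change in walk distance. The eligibility range has a half-width of (675 − 400)/2 = 137.5 m, but that is a between-person spread, not an SD of change. I therefore work in SDs of change. Suppose there is no true difference and one arm's mean is shifted by b SDs. For means (b, 0, 0) the noncentrality is λ = n × [(2b/3)² + 2(b/3)²] = 2nb²/3, with 2 and 3(n − 1) degrees of freedom. Rejection by the three-arm ANOVA at a nominal 5%:

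| b (assumed) | n = 8 per arm | n = 10 per arm |
|---|---|---|
| 0 | 5.0% | 5.0% |
| 0.1 | 5.3% | 5.5% |
| 0.2 | 6.4% | 6.8% |
| 0.3 | 8.3% | 9.3% |
| 0.5 | 14.7% | 17.8% |

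A shift that is equal in all arms leaves the rate at 5%. Here b is the shift in the arm mean. If only a fraction f of an arm is tested at the short gap and each of those loses e SDs, then b = f × e, so a short gap used by few participants matters less.

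**The case against.** The case on the other side is substantial.

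- **The usual gap is 48–72 h.** The 24 h gap is the permitted extreme, and the one consecutive pair allowed per week need not be sessions 35 and 36. This stands and limits the likely size.
- **The 48 h condition might be read to cover any third session of the week.** On that reading a 24 h gap before session 36 would be barred. The wording can bear it, but neither the example nor footnote a says so. An explicit rule for Visit 4 would settle the matter.
- **The contrast between an untrained baseline and a trained post-test is common to all arms.** A common shift cancels in the planned comparison. This stands; only an unequal effect matters.
- **The 48 h spacing in the protocol separates test visits from each other.** It is not a recovery rule between training and testing. This also stands. It is a convenient existing standard, not proof of an omission.
- **The Study Timeline text refers to Table 2, which is explicit, and 35 of 36 sessions are complete by Visit 4.** This makes the mismatch minor, but it is still a mismatch.

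A reader might go further and infer that RT would be the most fatigued arm. The predicted advantage of HIIT over RT on 6-min walk would then be favoured. The documents do not support this. HIIT in weeks 9–12 is also demanding, and its session 35 is one of the longer ones. If HIIT carried more fatigue, the bias would run the other way. For stair climb the protocol predicts similar change in all groups, so a loss confined to RT would work against its own prediction.

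A reader might also infer that anyone who misses session 36 loses the functional post-test. Visit 4 has its own day window, and handling of missed visits is a detail that a condensed article may leave to the full protocol.

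**Conclusion.** The point holds in a limited form. Two things are established from the text: the Abstract and Study Timeline disagree with footnote b on when the functional tests are repeated, and no minimum rest is set before Visit 4, so that testing about 24 h after session 35 is not clearly excluded.

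Differential residual fatigue is a possibility that follows from the different late-phase bouts. It is not demonstrated, and neither its direction nor its size can be derived from the document. The table of rejection rates shows only what an assumed one-arm shift would do: little at 0.1 to 0.2 SD, and a clear inflation at 0.5 SD.

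The reach is one secondary outcome (6-min walk) and the other functional outcomes. The primary outcomes are measured at Visits 5 and 6, after the last session, and this rule does not affect them. The plan also treats p-values as descriptive. The point merits correction because the remedy costs almost nothing, not because a large bias has been shown.

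**What to change.** - Schedule the Visit 4 functional tests at least 48 h after the preceding training session, in every arm. This matches the protocol's own spacing between test visits and its usual gap between sessions. It concerns the timing of an assessment and leaves the exercise prescription unchanged.
- Reconcile the Abstract and Study Timeline with footnote b, so that one statement says when the functional tests are repeated. If they are moved to a follow-up visit instead, apply the same spacing there.
- Reconcile footnote a of Table 2 with the Exercise Intervention section on consecutive days and the 24 h minimum, so that the permitted spacing has one reading.

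The cost is slightly less scheduling flexibility in week 12, plus wording corrections. No extra visit, test or participant is needed.

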### Outcome Measures

#### Primary Outcomes

##### Knee extensor isokinetic power

Maximal isokinetic power will be measured from the knee extensors. Peak torque will be recorded from the non-dominant leg using a Biodex System 4 Dynamometer (Biodex Medical Systems, Inc., Shirley, NY). The subject's leg will be immobilized against the lever arm with the distal end of the lever arm secured three inches superior to the medial malleolus. The axis of the lever arm will be centered at the lateral knee joint and knee range of motion will be obtained by having the subject extend their knee as far as possible against the lever arm. The maximal knee extension angle will be recorded, and the knee extension limit will be set 10° less than the maximal knee extension angle. The subject will then relax to allow the leg to return to neutral position and the knee flexion limit will be set at 80° of knee flexion. The speed of the lever arm will be set at 60°/s for both extension and flexion. The subject will then extend the knee with maximal effort until they reach the knee extension limit, and then immediately flex the knee with maximal effort until they reach the knee flexion limit. The time-series torque signal will be collected at 500 Hz by a Biopac MP150 system (Biopac Systems Inc., Santa Barbara, CA, USA). The subject will complete six isokinetic trials, with 30 s rest between trials. The average of the three highest peak torque values for both extension and flexion will be recorded at baseline and post-intervention, and percent change from baseline will be used for analysis.

##### Maximal oxygen uptake (VO_2_max)

VO_2_max will be obtained with a ParvoMedics TrueOne 2400 metabolic measuring system with a Hans Rudolf 3813 (Shawnee Mission, KS, USA) pneumotachometer to measure ventilation. The TrueOne 2400 is a mixing chamber system that uses a paramagnetic oxygen analyzer (range 0–25%) and an infrared, single beam, single wavelength carbon dioxide analyzer (range 0–10%). Prior to each test the system will be allowed to heat up for 30 min, and then will be calibrated according to the manufacturer's recommendations. This consists of a room air auto-calibration and a gas calibration with a single gas tank (16.00% O_2_, 4.008% CO_2_). Additionally, the flow meter will be calibrated with a 3.000-liter Hans Rudolf 5530 series syringe, with a 5-stroke calibration using different flow rates for each stroke. Ten ECG electrodes will be placed on the subject's body according to Mason-Likar procedures (54, 55). Prior to placement, the areas will be shaved with a disposable razor, wiped with an alcohol pad, and then lightly abraded with fine-grit sandpaper. The subject will be fitted with a Hans Rudolf Oro-Nasal reusable facemask (Shawnee Mission, KS, USA) with a 2-way non-rebreathing valve connected to the metabolic cart with large-bore, low-resistance tubing. The testing protocol will be explained to the subject, as well as how to communicate with investigators while wearing the facemask (i.e., hand signals). Resting VO_2_ values will be collected from the subject after 3 min of rest in a seated position on the cycle ergometer. Resting blood pressure will be taken immediately after resting VO_2_ is obtained. The subject will begin cycling on a magnetically braked cycle Lode Corival CPET ergometer (Lode B.V., Groningen, NL) at 60–80 RPMs (depending on subject comfort level) with a starting power output of 15 watts (W) for 1 min, collecting VO_2_ values every 20 s. Power output will be increased by 15 W every minute until subject can no longer continue the test or criteria have been met (Table 3). With 20 s remaining in each stage, the subject will indicate their RPE on a 6–20 Borg scale (56). With 10 s left in each stage, heart rate will be recorded from ECG readouts. Blood pressure will be taken at the beginning of even numbered stages. Subjects will be verbally encouraged throughout the test, and airflow will be provided through the use of a rotating fan. After test termination, the subject will perform a 5-min cycling cool down at 30 W. Blood pressure will be taken every 5 min for 20 min after the completion of the graded exercise test (GXT). Maximal heart rate will be determined from ECG readings during the final stage of the GXT for all subjects. Absolute VO_2_max measured in L/min will be recorded at baseline and post-intervention, and change from baseline will be used for analysis. Additionally, VO_2_max relative to body mass measured in mL/kg/min will be recorded at baseline and post-intervention, and change from baseline will be used for analysis.

**Table 3 T3:** Criteria for test termination during graded exercise testing.

**Criteria for maximal effort-related test termination**	**Criteria for health concern-related test termination**
•Subject requests to stop •Physical or verbal manifestations of severe fatigue •Failure of heart rate to increase with increased exercise intensity •Unable to maintain a cycle frequency of 50 RPMs for >5 sOr 2 of the 4 following criteria:•RPE of 17 or greater (Borg 6–20 scale) •Peak heart rate that is 85% of age-predicted maximal heart rate (220-age) •Plateau of VO2 •Respiratory exchange ratio (RER) of 1.1 or higher	•Angina or angina-like symptoms (subjective score of 2 or greater on ACSM angina scale) •Shortness of breath, wheezing, leg cramps, or claudication (subjective score of 3 or greater on ACSM claudication scale) •Signs of poor perfusion: light-headedness, confusion, ataxia, pallor, cyanosis, nausea, or cold and clammy skin •Drop in systolic blood pressure of >10 mm Hg, despite an increase in workload •Central nervous system symptoms (e.g., ataxia, dizziness, or near syncope) •Sustained ventricular tachycardia or other arrhythmia, including second- or third-degree atrioventricular block, that interferes with normal maintenance of cardiac output during exercise •Exaggerated hypertensive response (systolic blood pressure >250 mm Hg or diastolic blood pressure >115 mm Hg) •Abnormal changes in sinus rhythm •Exercise induced conduction blocks

*ACSM, American College of Sports Medicine; RPE, rating of perceived exertion; RPM, rotations per minute; VO2, volume of oxygen consumption*.

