### Sample Size

In this proof-of-concept, proof-of-mechanism trial, we report sample size estimates based on previous recommended literature (49). A sample size of ~8 subjects per group will detect a moderate effect. Sample size calculation was based on expected effect sizes for the HIIT cycle, MICT cycle, and RT groups for the primary outcomes of V0_2_max and thigh muscle CSA. Consistent with our “dual benefits hypothesis” we assumed, based on the literature, an 8% increase in thigh CSA for both the HIIT and RT groups (50) and 2% increase for the MICT group (51) and common SD across all groups of 4%. With the assumption of a 2-sided test and alpha level of significance equal to 0.05 an *n* = 7/group yields power of 0.83. With respect to VO_2_max we assumed a 32% increase in the HIIT group, a 15% increase in the MICT group, and a 10% increase in the RT group and common SD across all groups of 14% (52). With the assumption of a 2-sided test and alpha level of significance equal to 0.05 an *n* = 8/group yields power of 0.80. In line with other proof-of-concept, proof-of-mechanism trials, no statistical control for type-I error from multiple comparisons will be considered, and *p*-values will be interpreted with care, as descriptive weights of evidence rather than as confirmatory claims. Lastly, this proof of concept, proof of mechanism trial is needed to test the complex interventions proposed, and the effect sizes calculated from this trial could be used to estimate sample size for a future large-scale clinical trial. Accordingly, we plan to enroll an *n* = 8–10 subjects per group.

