##### MICT

The MICT will be performed on a stationary bicycle (Peloton Interactive, Inc. New York City, NY, USA) interfaced with a computer monitor that plays selected pre-recorded “spin classes.” Heart rate and power output are displayed in real time. The goal of MICT is to maintain an output that elicits the prescribed heart rate throughout the exercise session. Heart rate reserve (HRR) will be calculated by subtracting the subject's resting heart rate (obtained during medical history check at visit 1) from their maximal heart rate (obtained during the GXT). The progression of the 12-week program will go as follows. For the first week subjects will cycle for 20–30 min at 50–60% of their HRR. Week 2 subjects will cycle for 20–30 min at 55–65% of their HRR. Weeks 3–4 subjects will cycle for 30 min at 60–70% of their HRR. Weeks 5–8 subjects will cycle for 30–45 min at 65–75% HRR, and in weeks 9–12 subjects will cycle for 45 min at 70–75% HRR. These ranges are based on recommendations from a meta-analysis describing a dose-response relationship between exercise intensity and VO_2_max adaptations in older adults (64), An exercise supervisor will oversee each exercise session. The target output (in watts) will be determined during the first exercise session by having the subject cycle for 5 min at a cadence of 75 RPMs with a resistance that produces 50 W. Once a consistent heart rate is established (using a chest-strap heart rate monitor), we will increase or decrease the resistance until the target heart rate is maintained. The target output for each subsequent session will be the highest average output from the previous week. If there was no increase from the previous week, target average output will be manually increased by 3%. If the subject is maintaining the target output but not achieving the target heart rate, output will be increased incrementally by 2–5 W until the heart rate is maintained in the target range. During each exercise session the subject will follow the cadence recommendations of the spin class instructor (ranging 50–100 RPMs) while the in-person exercise supervisor modifies the resistance to ensure the output is maintained within the target range. At times the subject may be cycling at the target output but have a heart rate that exceeds the target. In these cases heart rate range takes precedence over output range, and output will be decreased until the target heart rate is maintained. This may occur when cycling at higher cadences (e.g., 90–100 RPMs). At the end of each exercise session subjects will be asked their perceived effort level for the entire session on a 1–10 scale and a Borg 6–20 scale. See Table 5 for exercise duration of each session.

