##### HIIT

Subjects in the HIIT group will use the same stationary bicycle setup as in the MICT group. The progression of the 12-week program will go as follows. Subjects will cycle continuously for 20–30 min at 50–60% of their HRR for the first week, and 20–30 min at 55–65% of HRR for the second week, similar to the MICT group. During the subsequent weeks, subjects will perform bouts of higher intensity cycling (target intensity of 80–100% of their HRR) interspersed with low- intensity rest periods (target intensity of 40–60% of their HRR). Here, the duration of the bout (or interval) will range from as little as 15 s and upwards of 1 min, and rest periods will be matched in a work/rest ratio of 2:1, 1:1, or 1:2 (1:1 on average). During weeks 3–4 the intensity will be at 80–95% of their HRR and the overall duration will last 15–20 min. Weeks 5–8 the intensity will be at 80–100% of their HRR with a duration of 15–30 min. During weeks 9–12 intensity will be at 85–100% of their HRR and duration will last 20–30 min. When the subject begins week three, the target average output will be determined by multiplying the subject's best average output from the first 2 weeks by 1.2. The subject will cycle at the target average output for the first 2–3 min of each session, at 150–300% of their target average output during the high-intensity intervals, and at 25–50% of their target average output during their low-intensity intervals in order to achieve the target heart rate ranges. The target average output for each subsequent week of exercise sessions will be the highest average output from the previous week. If there was no increase from the previous week, target average output will be manually increased by 3%. Subjects will complete 15, 20, or 30-min sessions throughout the study (Table 5) and will begin each session by cycling at the target average output for 2–4 min, followed by several high- and low-intensity intervals. Subjects will cycle at a high intensity for ~6 total min during 15 min sessions, ~8 total min during 20 min sessions, and ~10 total min during 30 min sessions, maintaining an average work/rest ratio of 1:1. The subject will follow the cadence recommendations (ranging 50–100 RPMs) of the spin class instructor while the in-person exercise supervisor modifies the resistance to ensure the output is maintained within the target ranges. It is unlikely that the subject's heart rate will reach 40–60% of HRR during the rest intervals, however, an output that is 25–50% of the target average output should elicit a heart rate that is 40–60% of HRR under normal conditions. Therefore, rest intervals will be long enough that the subject's heart rate will decrease by 5–20 beats per minute prior to the start of the next high-intensity interval. At the end of each exercise session subjects will be asked their perceived effort level for the entire session on a 1–10 scale and a Borg 6–20 scale. See Table 5 for exercise duration of each session.

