### Statistical Methods

The three intervention arms (HIIT, MICT, and RT) will be compared against each other for all primary analyses. For total fat mass and the primary and secondary knee extensor-related outcomes (isokinetic power, muscle volume, MVC, and isokinetic fatigue), we will compute a percentage change from baseline to 12 weeks. For absolute and relative VO_2_max and 6-min walk distance we will compute absolute change from baseline to 12 weeks. We will test differences in group means using one-way ANOVA with Sidak option in SPSS v. 25.0. Tukey *post hoc* tests will be performed if significant differences exist, alpha level set at 0.05. Additionally, as this is a proof-concept, proof of mechanism trial we will calculate effect sizes between groups using the corrected effect size Hedge's g with 95% confidence intervals for small sample sizes (65).

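### Table 3 can end the graded exercise test at two submaximal signs, so VO2max and the maximal heart rate behind both cycling arms' targets may be understated

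*Protocol article*

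**What the plan says.** The VO2max section of the protocol article describes a cycle test with 15 W added each minute "until subject can no longer continue the test or criteria have been met (Table 3"). The word 'or' makes the criteria an alternative to exhaustion. Table 3 is titled as a list of termination criteria. Its effort column gives four single reasons to stop and then allows a stop on "2 of the 4 following criteria": RPE of at least 17 on the 6-20 scale, "Peak heart rate that is 85% of age-predicted maximal heart rate (220-age"), a VO2 plateau, or RER of at least 1.1.

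Two quantities are taken from this test:

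- **VO2max**, a primary outcome. Under Statistical Methods, "we will compute absolute change from baseline to 12 weeks" for both its absolute and relative forms. Table 2 schedules the GXT at Visit 2 and Visit 5.
- **Maximal heart rate.** "Maximal heart rate will be determined from ECG readings during the final stage of the GXT for all subjects". The MICT section subtracts resting heart rate from the "maximal heart rate (obtained during the GXT") to obtain HRR. HRR then sets the targets in both cycling arms, for example 70-75% for MICT in weeks 9-12, while for HIIT "During weeks 9–12 intensity will be at 85–100% of their HRR".

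**The concern.** The four listed signs are reasonable evidence, after a test, that effort was high. As a live stopping rule they work differently. RPE 17 is three points below the top of its scale, and 85% of predicted heart rate lies below maximum for anyone whose true maximum is near prediction. Both can be present while the subject could continue, and neither a plateau nor RER 1.1 is then required. RPE and heart rate are both collected in the last 20 s of every stage, so the rule can be applied during the test. The article describes no verification bout and no requirement to continue past the criteria.

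Two things are at stake. A primary outcome may become VO2 at a threshold rather than at maximum. The training intensities, which carry the trial's central contrast, may also be scaled from too small an HRR.

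**Working it through.** **The plan's own figure.** The protocol gives no figure for early stopping. The nearest benchmark is the VO2max sample size: increases of 32, 15 and 10%, a "common SD across all groups of 14"%, and power 0.80 at n = 8 per group. For the omnibus one-way ANOVA, the mean is 19 and the squared deviations are 169 + 16 + 81 = 266. The noncentrality is 8 × 266 / 14² = 10.86 on 2 and 21 df, and power is 0.789, in line with the stated value.

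**Inputs.** From the protocol: ages 60-75, the 85% of 220-age criterion, and the HRR definition. Assumed, because the protocol does not give them: true maximum = 220-age, age 67, resting heart rate 70, resting VO2 3.5 mL/kg/min, true VO2max 15 to 30 mL/kg/min, and heart rate and VO2 rising together linearly from rest to maximum.

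**Step 1: fraction of HRR recorded.** With a stop at proportion p of predicted heart rate, f = (p × 153 − 70) / (153 − 70).

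- p = 0.85: 60.05 / 83 = 0.72
- p = 0.90: 67.7 / 83 = 0.82
- p = 0.95: 75.35 / 83 = 0.91

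Over ages 60-75 and resting rates 60-80, f at p = 0.85 runs from 0.67 to 0.76. If the true maximum is 10 bpm below prediction, f = 60.05 / 73 = 0.82, so the error is smaller. If it is above prediction, the error is larger.

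**Step 2: VO2max recorded.** The ratio to true is [3.5 + f(V − 3.5)] / V for V = 15 and V = 30.

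| Stop (p) | f | Recorded / true VO2max |
|---|---|---|
| 0.85 | 0.72 | 0.79 to 0.76 |
| 0.90 | 0.82 | 0.86 to 0.84 |
| 0.95 | 0.91 | 0.93 to 0.92 |

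**Step 3: effect on change, for one subject.**

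- *Early stop at baseline only, p = 0.85:* false rise = 1/ratio − 1 = 27 to 32%.
- *Early stop at post-test only, p = 0.85:* false fall = 1 − ratio = 21 to 24%.
- *Same stop at both visits:* absolute change is multiplied by f (0.72 at p = 0.85). Percent change is multiplied by f / ratio, which is 0.723/0.788 to 0.723/0.756, or about 0.92 to 0.96.

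A false rise of 27 to 32% in one subject of a group of 8 moves that group's mean by 27/8 to 32/8, about 3.4 to 4.0 percentage points.

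**Step 4: effect on nominal training targets (weeks 9-12), as a percentage of true HRR.**

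| Stop (p) | HIIT 85-100% becomes | MICT 70-75% becomes | MICT ceiling to HIIT floor (0.10 × HRR) |
|---|---|---|---|
| 0.85 | 62-72 | 51-54 | 6.0 bpm |
| 0.90 | 69-82 | 57-61 | 6.8 bpm |
| 0.95 | 77-91 | 64-68 | 7.5 bpm |
| none | 85-100 | 70-75 | 8.3 bpm |

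The arms stay apart in every row, because both targets shrink by the same factor.

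**The case against.** Several counter-arguments have force.

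**The extremes are conditional.** The 85% row needs a true maximum near 220-age, RPE 17 already at about 72% of true HRR, and staff who stop at once although the protocol asks for encouragement throughout. Many tests would end through fatigue, or with a plateau or high RER. This stands: the figures are bounds, and at a 95% stop the loss is modest.

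**A reader might infer a biased comparison between arms.** The documents do not support that. One rule applies to all arms at both visits, so bias would need early stopping that differs by arm, and nothing in the protocol gives its direction. Nor can the 27-32% false rise be set directly against the 17-point HIIT-MICT difference (32 − 15), since one is a single-subject extreme and the other a difference in group means.

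**Uniform truncation does limited analytic harm.** Under the same linear model, group differences and the true spread of change shrink together. The ANOVA F and Hedges' g are then largely unchanged, apart from measurement noise that does not shrink. This stands, and it is why the factor of 0.72 on absolute change should not be read as an equal loss of power.

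**A reader might infer that HIIT would actually be delivered at 62-72% of true HRR.** That range converts the nominal target only. HIIT intervals are also set at 150-300% of a target average output that is carried forward weekly, and raised 3% if there was no increase. The protection is partial: the week 3 target is 1.2 times the best average output of weeks 1-2, when load was guided by the same HRR. MICT is more exposed, because its heart rate range overrides output.

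**85% is not a general floor.** It is the earliest stop only for pairs that include the heart rate criterion. RPE with RER has no such floor. Conversely, a subject whose true maximum is below 85% of 220-age never meets the heart rate criterion.

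**Staff may already use the list as a post-test check.** They may, but the text and the table title make it a stopping rule.

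**Conclusion.** The point holds as a statement about what the written rule permits: a GXT run exactly as described can end before maximum, and no other part of the article overrides this. For a single subject, under the assumptions above, a stop at 85 to 95% of predicted heart rate records 72 to 91% of true HRR and roughly 76 to 93% of true VO2max. An early stop at one visit only creates a false change for that subject and adds noise to a trial with 8-10 per group. The same early stop at both visits costs little on the percent scale (4-8% of the change at the 85% stop) or in standardized differences. Nominal HRR targets fall by the same fraction in both cycling arms, with MICT the more exposed.

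The frequency is unknown and the direction of any between-arm bias cannot be derived, so this is no ground for calling the comparison invalid. It is a cheap improvement, though more than a wording matter, because it affects what a primary outcome measures and how training is dosed.

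**What to change.** Remove the 2-of-4 set from the termination column of Table 3 and adjust the sentence in the VO2max section to match. Suggested text:

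> The test ends when the subject asks to stop, shows severe fatigue, has no further rise in heart rate as load increases, cannot hold 50 RPM for more than 5 s, or meets a health criterion. After the test, effort is classed as maximal if at least two of these were reached: RPE ≥17, 85% of age-predicted maximal heart rate, a VO2 plateau, RER ≥1.1. The same procedure applies at Visit 2 and Visit 5.

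This needs no extra visit or equipment. Tests that would have been stopped early run a few 1-min stages longer. The real cost is that more insufficiently active subjects aged 60-75 reach volitional exhaustion. They would do so under the ECG and blood-pressure monitoring and the health-stop rules already in place.
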